#### Familiarisation

The participants will be required to complete a familiarisation session at least two weeks prior to their main trials. The familiarisation visit will involve participants completing the main exercise protocol procedures to be performed during the trial (described in the experimental protocol) but without any collection of tissue samples. This visit, therefore, allows participants to familiarise with the study procedures and, thus, diminish any learning/trial-order effects. This visit will also enable us to confirm that the calculated running speeds reflect the required intensity (that is, 60% and 70%
$\bar{V}O_{2\max}$) during the trial, with any adjustments to speed deemed by expired gas data being applied accordingly.

### Physiological measurements

#### Urine output

Baseline urine samples will have been obtained 30 minutes before testing to determine hydration via the freezing point depression method by using a cryoscopic osmometer (Advanced Instruments, Inc, Norwood, MA, USA). The threshold for adequate hydration will be assumed for osmolality values ≤900 mOsm.kg^-1^[51]. During the four hour recovery period, the voided urine will be collected in a vessel containing a preservative (5 ml of 10% thymol isopropanol). Upon recording total urine output during this period, a mixed 1 ml sample will be taken and stored at -80°C to enable the estimation of total urinary urea nitrogen excretion, which will subsequently be corrected with plasma urea for whole-body determination of the urea pool during recovery
[52]. Non-protein respiratory exchange ratios (NPRER) will also be calculated to reflect protein oxidation rates during the four hour recovery phase
[53].

#### Expired gas sampling

Expired gas samples will be obtained via the Douglas bag method (Hans Rudolph, Shawnee, KS, USA) from each participant. A respiratory valve with a mouth piece will be attached to a 200 litre Douglas bag for expired gas sampling, which will be provided with a nose clip to participants approximately 30 seconds before sampling to remove any residual atmospheric air from the valves. The collected gas samples will then be analysed for relative expired fractions of oxygen and carbon dioxide using paramagnetic and infra-red analysers, respectively (Servomex, Crowborough, UK). The total volume of expired gas within the Douglas bag will subsequently be measured by a dry gas meter (Harvard Apparatus, Kent, UK), with the temperature of expired gases being collected at the time of evacuation by a thermistor probe. Prior to any gas collection, calibration of equipment will be conducted using gas cylinders containing specific gases with a known relative composition (N_2_ = 0%; O_2_ = 16.9%; CO_2_ = 4.93%), as validated by the manufacturer (CryoService, Worcester, UK). Each analyser will then be validated against atmospheric air. The inspired air will be measured proximally to the participants throughout the studies, with values used relative to each corresponding expired gas sample to minimise systematic bias associated with assumptions that inspired gas fractions are stable and reflective of atmospheric constants
[54].

The calculations of oxygen consumption and carbon dioxide production from each bag will then be used for the determination of carbohydrate and lipid oxidation rates (g.min^-1^) using the following formulae:

$$\begin{array}{l} \text{Carbohydrate}\;\text{Oxidation}=\left(4.212\;\times \;{\text{VCO}}_{2}\right)-(3.005\;\times {\mathrm{VO}}_{2}\;)-(2.449\;\times \;N)\\ \text{Fatty}\;\text{Acid}\;\text{Oxidation}=\left(1.754\;\times {\mathrm{VO}}_{2}\right)-(1.754\;\times \;{\mathrm{VCO}}_{2})-(2.017\;\times \;N) \end{array}$$

Where N is the estimated rate of nitrogen excretion based on urinary/plasma urea
[52].

Extramuscular carbohydrate oxidation can then be derived from the difference between whole-body carbohydrate oxidation as determined from indirect calorimetry and intramuscular carbohydrate oxidation methods (overall muscle glycogen degradation rates).

#### Blood sampling

During the familiarisation session, blood samples will have been obtained using the capillary fingertip method by a 3 mm puncture (Accu-Check; Roche Diagnostics GmbH, Mannheim, Germany) applied distally relative to each participant’s fingers. These will be dispensed into microvettes (approximately 25 μl) containing lithium heparin to act as an anticoagulant before being analysed for blood glucose and ketone body concentrations (Optium Xceed; Abbott Laboratories Ltd., Maidenhead, UK). Venous blood samples will have been obtained during the main trials via an indwelling cannula; inserted into an antecubital vein under local anaesthesia (1% lidocaine; Hameln Pharmaceuticals Ltd., Brockworth, UK) and kept patent throughout the trials by flushing with heparin-free isotonic saline (B. Braun, Melsungen, Germany) following each sampling point. Participants will be rested in a semi-supine position for 10 minutes prior to any baseline blood sample. A 10 ml blood sample will be collected during each sampling point before being dispensed into 2 × 5 ml tubes. Each blood sample will first be transferred into a non-anticoagulant collection tube (Sarstedt, Leicester, UK), and left to clot for approximately 45 minutes at room temperature before centrifugation at 2000 × g for 10 minutes at 4°C (Heraeus Primo R; Thermo Fisher Scientific, Loughborough, UK) for serum extraction, which will be stored at -80°C pending analysis for insulin concentration. The remaining 5 ml of each venous blood sample will be dispensed into a different tube containing an anti-coagulant (ethylenediaminetetraacetic acid; EDTA) then immediately analysed for haemoglobin concentrations by using an automated haematology analyser (Sysmex SF-3000; Sysmex Ltd., Wymbush, UK). Thereafter, 3 × 50 μl aliquots of blood will be removed using micro-haematocrit tubes and subsequently centrifuged (Hawksley, Lancing, UK) to obtain haematocrit concentrations. Equations based on heamoglobin and haematocrit values will be utilised to determine plasma volume changes throughout the trials
[55]. The remaining EDTA-treated blood will then be spun for centrifugation under 2000 x g for 10 minutes at 4°C for plasma extraction prior to being stored at -80°C for later analysis of plasma glucose, lactate, non-esterified fatty acids and urea.

#### Plasma glucose, lactate, non-esterified fatty acids and urea

For the assessment of plasma metabolites, an automated spectrophotometric analyser (RX Daytona, Randox, Crumlin, Ireland) will be utilised. Prior to each sample analysis a calibration will be conducted and quality control will be checked against the manufacturer’s available standards.

#### Serum insulin

Sera concentrations will be assessed by enzyme-linked immunosorbent assays (ELISA) using a spectrophotometric plate reader. The fundamental principle of all these assays is that the target analyte (the antigen) is recognised with high specificity by antibodies within the human body. The immune system produces antibodies in response to the presence of antigens. These antibodies subsequently recognise and bind to the antigens, and the labeling of the resultant bound antibody forms the basis of this method
[56].

#### Muscle biopsy sampling and storage

To minimise discomfort for participants while obtaining muscle samples at essential time points for the aims of the study, three muscle biopsy samples will be obtained during each main trial. In Phase I and during the low sucrose treatment arm, a muscle biopsy sample will be taken at the point of volitional exhaustion following the first exercise bout to identify muscle glycogen depletion levels before the short-term recovery period. Indeed, given that participants had consumed replicate diets 48 hours prior to each main trial and the provision of a standerdised final meal (see standardisation of lifestyle section), and were required to run to volitional exhaustion suggests that muscle glycogen levels are expected to be similar between any of the first exhaustive exercise bouts during the main trials. Based on previously reported data that applied a similar dietary and activity standardisation in addition to comparable exercise protocol procedures, it was shown that muscle glycogen depletion levels were unlikely to vary between trials
[38]. Hereafter, a biopsy sample will not be required at this time point during the high sucrose trial. Further support of this is gained through the initial run times to exhaustion obtained from participants tested thus far in Phase I, indicating comparable times to exhaustion (data not shown) and, thus, endorsing the notion that intra-individual pre- and post-exercise muscle glycogen contents were at comparable levels between the trials. The remaining two biopsy samples in the low sucrose treatment will be obtained at the end of recovery and at the point of fatigue during the subsequent run. During the high sucrose treatment, the three muscle tissue samples will be obtained at the end of the recovery period, the time corresponding to fatigue during the low sucrose treatment and at the point of volitional exhaustion during the subsequent run.

It is difficult to ascertain the condition under which muscle glycogen storage and/or endurance capacity may be enhanced in Phase II of the trial. Therefore, three biopsies will be obtained at identical time points between the treatment arms to assess relative glycogen resynthesis rates during recovery and their degradation rates during the subsequent exercise bout. To achieve the aforementioned aims, the biopsy time points will be: following the first exhaustive run, at the end of the four hour recovery period and upon cessation of the subsequent run to exhaustion.

A needle biopsy technique
[57] will be used to obtain approximately 30 to 100 mg of wet muscle tissue from the *vastus lateralis*. This specific site was chosen: (1) to present muscle glycogen data that are comparable with the majority of investigations conducted in this area; and (2) because of the large contribution of the quadriceps muscles during treadmill running. Although it was demonstrated that muscle glycogen utilisation is greater in the calf muscles than in the thigh muscles
[58], it is clear that substantial depletion of muscle glycogen in the quadriceps is present during treadmill running
[38] Thus, measurements obtained from the *vastus lateralis* were assumed to reflect the total contribution of muscle glycogen towards overall metabolism under the assumption that dry muscle mass of both legs was 5% of body mass and that glycogen utilisation of these limbs is represented by the *vastus lateralis* sample. Each muscle sample will be taken from a different 3 to 5 mm skin incision site separated by 2 to 3 cm and applied under a local anaesthetic (2 to 3 ml of 1% lidocaine, Hameln Pharmaceuticals Ltd., Brockworth, UK) while participants were in a semi-supine position. An opposite leg will be used during the second main trial for each participant, where the use of dominant/non-dominant limbs will be counterbalanaced between participants.

#### Muscle biopsy analysis

Once removed from the leg, the muscle tissue will be extracted immediately from the needle biopsy and snap-frozen into liquid nitrogen. The muscle samples will then be removed and placed in a cryogenic vial (Corning, Ewloe, UK) while being maintained in liquid nitrogen where they will be subsequently stored at -80°C pending analysis for muscle glycogen concentrations determined spectrophotometrically
[59].

#### Decontamination procedures

Once the wet muscle tissue extraction process has been completed, all equipment used in the muscle biopsy technique will undergo a generic decontamination procedure. All muscle biopsy component parts will be disassembled and cleaned individually with warm water. A wire brush will then be used to remove any organic matter, blood or any other deposits prior to being placed in an Ultrasonic bath containing a solution of 0.3% Sonozyme enzymatic soap for sonification for 10 minutes at 30°C. Once sonified, all equipment will be rinsed with ultrapure water before being immersed in a disinfectant (Milton Sterilising Tablets, Newmarket, UK) for 15 minutes before another rinse cycle with deionised ultrapure water. Finally, each item will be individually placed in a sterilising pouch prior to an autoclave at 121°C for 20 minutes.

#### Subjective measurements

Subjective RPEs will be obtained during all exercise trials by using Borg’s 6 to 20 RPE scale
[49], where 6 and 20 range from ‘very very light’ to ‘maximum’ effort. Subjective measurements of stomach discomfort, gut fullness and thirst will be recorded using adapted Borg scales in which scales ranged from ‘no discomfort’ to ‘extreme discomfort’, ‘not full’ to ‘very very full’ and ‘not thirsty’ to ‘very very thirsty’, respectively. To account for any mood disturbances during any experiments, a POMS questionnaire will be completed by each participant prior to commencing any of the trials. This questionnaire has been shown to be a viable tool to detect any mood fluctuations in an exercise setting that may have an influence on performance
[60,61].

#### Reliability measurements

To evaluate the error variation and establish sufficient precision of measurement, coefficients of variation (CV = SD/mean × 100) will be assessed for intra-assay and intra-gas variations upon the attainment of data from our procedures.

### Statistical analysis

While the primary outcome measure in these experiments is the rate of muscle glycogen resynthesis/degradation, this variable is highly reliable relative to other outcomes and, accordingly, this consistency results in sample size estimates requiring only four or five participants (thus justifying the use of typically six or eight participants in most studies in this field). It was, therefore, deemed appropriate to base sample size estimates on secondary, less reliable, outcome measures. In this case, exercise capacity exhibits the highest between subject variability and our previous work that contributes directly to the rationale for this study observed a difference between the high sucrose and moderate sucrose plus whey protein supplements under investigation here of 7.5 minutes, with a standard deviation of differences of 5 minutes
[21]. Based upon these data, it can be estimated that a sample size of seven would be appropriate even to provide a 90% power to detect such effects on these more variable secondary outcomes using a two tailed paired *t*-test.

A paired *t*-test will be used to compare between treatments for the primary and secondary outcomes of the study (that is, glycogen resynthesis/degradation and run times to exhaustion). A two-way linear mixed model with repeated measures (beverage × time) will be employed to analyse the repeated experimental conditions. Mauchly’s test will be used for sphericity. Where asphericity is assumed, the Greenhouse-Geisser correction will be used for epsilon <0.75 and Huynh-Feldt will be adopted for less severe asphericity. Where significant F values are found a Bonferroni step-wise correction will be employed to determine the location of the variance
[62]. Simple summary statistics will be used to inform interesting questions related to certain metabolites (for example, plasma glucose) following each feeding strategy and during the subsequent exhaustive bout. Statistical procedures were performed using commercially available software (IBM SPSS version 20.0, SPSS Inc., Chicago, IL, USA) and significance is set at an alpha level of 0.05. All results will be reported as the mean ± standard deviation (SD) of the mean unless stated otherwise.

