**Methods/Design:**

The project involves two phases with each involving two treatment arms administered in a repeated measures design. For each treatment, participants will be required to exercise to the point of volitional exhaustion on a motorised treadmill at 70% of previously determined maximal oxygen uptake, before a four hour recovery period in which participants will be prescribed solutions providing 1.2 grams of sucrose per kilogram of body mass per hour of recovery (g.kg^-1^.h^-1^) relative to either a lower rate of sucrose ingestion (that is, 0.3 g.kg^-1^. h^-1^; Phase I) or a moderate dose (that is, 0.8 g.kg^-1^.h^-1^) rendered isocaloric via the addition of 0.4 g.kg^-1^.h^-1^ whey protein hydrolysate (Phase II); the latter administered in a double blind manner as part of a randomised and counterbalanced design. Muscle biopsies will be sampled at the beginning and end of recovery for determination of muscle glycogen resynthesis rates, with further biopsies taken following a second bout of exhaustive exercise to determine differences in substrate availability relative to the initial sample taken following the first exercise bout.

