### Trial design

The methods described here stem from a wider project titled ‘Macronutrient ingestion, Muscle glycogen and Post-Exercise Recovery’. Both trial phases described herein have been approved by the National Health Service (NHS) South West 3 Research Ethics Committee (REC) with an allocated reference number: 09/H0101/82. The project was subsequently registered as a clinical controlled trial (ISRCTN 87937960).

Phase I of testing will address objective (i) by way of a non-randomised repeated measures design. The chosen trial design for Phase I is based on the premise that a lower rate of sucrose ingestion will mediate sub-optimal recovery, thus resulting in impairment in exercise capacity relative to a higher rate of sucrose intake, as has been previously reported in a similar investigation
[21]. It was, therefore, assumed that participants would run longer when the higher sucrose treatment was administered. Accordingly, a non-randomised design would allow not only an investigation of the metabolic environment at the point of fatigue during the low versus high sucrose treatments, but also at the time point in the high sucrose treatment coincident with the onset of fatigue during low sucrose treatment. Indeed, previous studies have adopted a similar approach to investigate mechanisms through which carbohydrate supplementation enhances the capacity for both cycling
[37] and running
[38] modes of exercise. In addition, participants will be fully familiarised with a trial (see experimental protocol) that will be identical to the main procedures and, therefore, diminishing any order effects. This will consequently improve the reliability of the performance measure that would enable the detection of small but worthwhile intervention effects
[39].

The second phase (Phase II) of testing will address objective (ii) by adopting a randomised double-blind cross-over experimental design.

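### Phase II is a randomised, counterbalanced two-period cross-over, but its paired t-test has no period term; the loss is conditional on a period effect and the remedy costs one degree of freedom

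*Protocol article*

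**What the plan says.** The Trial design section states: "The second phase (Phase II) of testing will address objective (ii) by adopting a randomised double-blind cross-over experimental design". The Methods/Design part of the abstract adds that the Phase II treatments are given "as part of a randomised and counterbalanced design". Phase I, by contrast, is non-randomised with a fixed order.

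The Statistical analysis section names one between-treatment test, without distinguishing the phases: "A paired *t*-test will be used to compare between treatments for the primary and secondary outcomes of the study". The sample size of seven for 90% power also rests on "using a two tailed paired *t*-test", and "significance is set at an alpha level of 0.05". The only other model is for the serial measurements: "A two-way linear mixed model with repeated measures (beverage × time) will be employed to analyse the repeated experimental conditions". Neither analysis names a period or sequence factor.

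The article takes several steps against order effects: a familiarisation visit, a wash-out of at least two weeks, and replicated diet and activity. It also reports a between-trial CV of 3.5% for time to exhaustion in the first run.

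**The concern.** In a two-period cross-over, each participant's treatment difference is the treatment effect plus or minus the period effect, with the sign set by the sequence. Balanced sequences cancel the period effect from the mean difference but not from the spread of the differences. A plain paired t-test counts that spread as random error. The design lets period be separated from treatment, and the planned test does not use this.

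A residual first-to-second-trial change is credible on the article's own description. The Trial design section presents familiarisation as the same as the main procedures, but the Familiarisation section says no tissue is collected, and the Blood sampling section says fingertip samples replace the cannula. The first main trial is thus the participant's first experience in this study of biopsies and cannulation around an exhaustive run. The main trials are also at least two weeks apart. At stake are power, interval width and, after an unbalanced dropout, a small bias.

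**Working it through.** **Inputs from the article.** Treatment difference 7.5 min, SD of within-participant differences 5 min, two-sided alpha 0.05, n = 7 for 90% power (Statistical analysis); eight participants per phase (Participants).

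**Assumptions.** Sequences split 4/4 at n = 8 and 4/3 at n = 7; normal differences; no carry-over. The article gives no period effect, so a range of 0 to 5 min is shown.

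**Step 1: the plan's own figure.** For a paired t-test the noncentrality is (7.5/5)·√n with n − 1 degrees of freedom. Exact power is 83.3% at n = 6, 90.8% at n = 7 and 95.1% at n = 8. The stated n = 7 for 90% power reproduces.

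**Step 2: the two analyses.** Let τ be the treatment effect, π the period effect and σ the SD of differences within a sequence. A participant's treatment difference is d = τ ± π + error.
- Paired t: the estimate is the mean of all d, with n − 1 df. At 4/4 the expected variance of d is σ² + (8/7)π². With σ = 5, the SD becomes √(25 + 8/7 × 9) = 5.94 min at π = 3 and √(25 + 8/7 × 25) = 7.32 min at π = 5.
- Period-adjusted: the estimate is the average of the two sequence means of d, with standard error s·√[(1/n₁ + 1/n₂)/4], s pooled within sequences, and n − 2 df. π cancels from both the estimate and s.

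**Step 3: reading A, the 5 min SD excludes any period effect (n = 8, 4/4).** Power and type I error by simulation, 400,000 and 200,000 trials per setting; power at 0 min agrees with the exact calculation.

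| Period effect (min) | Paired t power | Adjusted power | Paired t true type I error |
|---|---|---|---|
| 0 | 95.1% | 93.9% | 5.0% |
| 1 | 94.6% | 93.9% | 4.6% |
| 1.5 | 93.8% | 94.0% | 4.3% |
| 2 | 92.7% | 93.9% | 3.6% |
| 3 | 89.2% | 93.9% | 2.4% |
| 4 | 83.5% | 93.9% | 1.4% |
| 5 | 75.4% | 93.9% | 0.7% |

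The adjusted test keeps about 5.0% type I error throughout. Break-even is near 1.5 min, which is 0.3 of the SD of differences (1.5/5).

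**Step 4: reading B, the 5 min SD already contains the period effect.** The within-sequence SD is then √(25 − (8/7)π²), so π cannot exceed √(25 × 7/8) = 4.68 min. Power, paired versus adjusted: 95.1% vs 93.9% at 0 min, 95.3% vs 94.8% at 1 min, 96.2% vs 97.2% at 2 min, 97.8% vs 99.5% at 3 min.

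**Step 5: one dropout (n = 7, 4/3), σ = 5.** The paired estimate is biased by (4 − 3)/7 × π = π/7: 0.43 min at π = 3 and 0.71 min at π = 5. Simulated power, paired versus adjusted, is 90.7% vs 87.6% at 0 min, 88.1% vs 87.6% at 2.5 min, 86.4% vs 87.7% at 3 min and 74.5% vs 87.6% at 5 min.

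**The case against.** The strongest case is that the loss is hypothetical. No section reports a period effect, and 5 min equals a full SD of the differences. Familiarisation, wash-out and lifestyle control are all aimed at order effects. Below about 1.5 min the planned test is slightly the more powerful. Under reading B its power stays at about 95% or higher. At n = 7 split 4/3, adjustment takes power from 90.7% to 87.6% when there is no period effect, below the stated target. The 4/3 bias at a 3 min period effect, 0.43 min, is small beside a standard error of about 5/√7 = 1.9 min. All of this stands, and it sets how the point must be worded.

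A reader might infer that the plan is discarding power, or that the paired test is invalid. The documents support neither. The first needs a period effect above break-even, which no section reports. The second fails because at 4/4 the estimate is unbiased and the true type I error is at or below 5%.

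Two parts of the objection carry less weight. The 3.5% CV concerns the first run, before feeding and before any biopsy, so it does not bound a period effect on the second run. And although a condensed article may leave model detail to a fuller plan, this one does not leave the test open: it names the paired t-test for primary and secondary outcomes.

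**Conclusion.** The point holds in conditional form, for Phase II only. The design allows period to be separated from treatment and the named test does not do so. Whether this costs anything depends on a period effect that the article does not give and on whether the 5 min SD already includes one. Under reading A, adjustment gains 4.7 points at 3 min (93.9 − 89.2) and 18.5 points at 5 min (93.9 − 75.4), and loses 1.2 points at 0 min (95.1 − 93.9). Under reading B the 90% target is safe and adjustment gains only from about 2 min.

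All figures concern time to exhaustion, which is a secondary outcome. The article gives no effect or SD for glycogen resynthesis or degradation, so nothing is quantified for the primary outcome. Phase I is outside the point: with a fixed order, period cannot be separated from treatment. This is a cheap improvement to efficiency and robustness, not the correction of an invalid analysis.

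**What to change.** For Phase II, replace the paired t-test by the two-period cross-over analysis. Use either a mixed model with treatment and period as fixed effects and participant as a random effect, or the equivalent two-sample t-test on within-participant period differences by sequence. If the sponsor prefers the paired test, the plan should justify omitting period.

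The change is one sentence and needs no extra participants, visits or measurements. The Trial status section has Phase II still recruiting, so on the article's own account the term can be fixed before analysis.

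The cost is one degree of freedom. With no period effect, power for time to exhaustion falls by about 1 point at n = 8 (95.1% to 93.9%) and about 3 points at n = 7 split 4/3 (90.7% to 87.6%). The planned eight participants still meet the 90% target after adjustment; seven would not.
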